**Figure 2 F2:**
[figure not shown]
Overview of preferable study contact moments for patients. *The interview will be held with the first 10 patients and informal caregivers in the hospital-at-home group (and general practitioners), the nursing home group and the control group. **Informal caregivers and treating physicians will also receive a phone call at 30 days.

**Table 3 T3:** Overview of the data collection at the different time points

	Day 1	Day 2	Day 7	Weeks 2–3	30 days	6 months	12 months
Mortality	X	X	X		X	X	X
KATZ-15	X				X	X	X
Living situation	X				X	X	X
EQ-5D-5L	X				X	X	X
Demographics	X						
Charlson Comorbidity Index	X						
G-8 screening tool	X						
6-item Cognitive Impairment Test	X						
Core Consensus Sleep Diary	X	X	X				
PROMIS Sleep Disturbance short form 8b			X		X		
Satisfaction				X^*^	X^†^		
Complications					X		

*An interview will be held with the first 10 patients and informal caregivers in the hospital-at-home group (and general practitioners), the nursing home group and the control group.

†Questionnaires will be conducted with the patients, their informal caregivers and their treating physicians.

PROMIS, Patient-Reported Outcomes Measurement Information System.

#### Semi-structured interview after 2–3 weeks

After 2–3 weeks of inclusion, a semi-structured in-depth interview will be held on voluntary basis with the first 10 patients included in the hospital-at-home group, nursing home group and control group. If these 10 patients in each group agree to participate in the interview, their informal caregivers will also be asked if they want to participate in a similar interview to collect information about their experiences. The interview of the patient and their informal caregiver can take place simultaneously. If the patients in the hospital-at-home group agree to participate in the interview, their GPs will also be asked for an interview to collect information about their experiences with the care pathway. This interview with the GP will take place separately. By selecting participants in this way, the interviews will be taken without purposive sampling.

The framework that is used to develop the interview guide is the Consolidated Framework for Implementation Research (https://cfirguide.org), which provides a framework of constructs that are associated with effective implementation.^39–41^ There are five domains with corresponding example questions. These questions have been adapted and tailored to the intervention programme and will form the basis for a process evaluation of the implementation of the care pathway focusing on the implementation, the mechanisms of impact and context (facilitators/barriers to implementation).^42^ The information collected during these interviews will be used to adjust the care pathway.

#### Study phone calls at 30 days

At 30 days, all patients will receive a phone call (or visit at request of the patient) from a research team member in which they will be asked about the occurrence of complications (readmissions, delirium, falls), their sleep quality (PROMIS Sleep Disturbance short form 8b), functional status (KATZ-15 and living situation), QoL (EQ-5D-5L) and satisfaction. The questions to evaluate satisfaction are based on the Consumer Quality Index, Patient Reported Outcome Measures and other research evaluating the out-of-hospital treatment of patients and adjusted if applicable.^43 44^

At 30 days, all informal caregivers and treating physicians will receive a phone call from a research team member in which they will be asked about the satisfaction, usability and acceptance of the care pathway. In this call, treating physicians will also be asked about the occurrence of complications.

#### Study phone call at 6 and 12 months

At 6 and 12 months, all patients will receive a phone call (or visit at request of the patient) from a research team member in which they will be asked about their functional status (KATZ-15 and living situation) and QoL (EQ-5D-5L).

The research group has longstanding experience performing questionnaires by telephone in the older population, which has proven to be feasible and was validated in previous studies.^45^

### Data analysis plan

The primary outcome is the feasibility of the care pathway. This will be quantitative data. Categorical variables will be presented as counts and frequencies. The quantitative data will be analysed with the Statistical Package for the Social Sciences (SPSS) V.28.

The secondary outcomes will be established by comparing the patients in the care pathway group with the patients in the control group during follow-up. Secondary outcomes are the safety of the care pathway (30-day mortality and occurrence of complications within 30 days); the satisfaction, usability and acceptance of the care pathway; the total number of days of bedridden status or hospitalisation; sleep quantity and quality; functional outcomes and QoL.

Categorical variables will be presented as counts and frequencies. Differences between groups will be tested with χ^2^ tests and multivariate logistic regression models. Continuous data will be presented as means (standard deviations) for normally distributed data or medians (interquartile ranges) for non-normally distributed data. Differences between groups will be tested with independent t-tests or one-way Analysis Of Variance (ANOVA) tests (normal distribution), or Mann-Whitney U or Kruskal-Wallis tests (no normal distribution) depending on the amount of groups to be compared per analysis, and by multivariate linear regression models. All tests of significance will be at two-tailed 0.05 level. The 95% confidence intervals will be used to assess the presence/absence of associations. The quantitative data will be analysed with SPSS V.28.

All recorded interviews will be transcribed by two research team members and hereafter then coded with Atlas.ti V.22. The interview recordings will be saved in a secured folder on the network of the coordinating hospital and will be deleted after verbatim transcription. Transcriptions will be saved on the network of the coordinating hospital. We will apply thematic content analysis to identify and categorise recurrent themes/elements in the interviews. Thereby, we aim to classify the qualitative data in the right sections (implementation, methods, context) of the process evaluation of the implementation of the care pathway.

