### Sample size

Ideally, 50 patients will be treated outside the hospital (care pathway group) and 50 patients will be treated in the hospital (control group). A power analysis was performed for the evaluation of the feasibility of the care pathway. In clinical practice, approximately 10% of the hospitalised patients are readmitted to the hospital after discharge. Our hypothesis is that in at least 75% of the older adults with an acute LRTI or pneumonia who are treated outside the hospital (at home or in a nursing home) according to the care pathway (care pathway group), hospitalisation can be avoided (complete treatment outside the hospital during 30-day follow-up). An 80% power with an alpha of 0.05 for an one-sample study will be achieved if 40 patients are recruited for the care pathway group.

For the qualitative endpoints, data collection (interviews) will be performed until data saturation is reached. When a patient is included and his/her informal caregiver and/or treating physician does not want to participate or cannot participate in the study, the patient will remain in the study and no extra patient will be included to make up for the missing informal caregiver and/or physician.

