### Outcomes

The primary outcome is the feasibility of the care pathway, which is defined as the percentage of patients treated outside the hospital, according to the care pathway, whom fully complete their treatment without the need for hospitalisation within 30 days of follow-up. This will be measured by the amount of hospitalisations within 30 days of follow-up in patients treated outside the hospital.

The secondary outcomes are the safety of the care pathway (30-day mortality and occurrence of complications (readmissions, delirium, falls) within 30 days); satisfaction, usability and acceptance of the care pathway (30-day satisfaction questionnaires (patients, informal caregivers and treating physicians) and semi-structured in-depth interviews with the first 10 patients and their informal caregivers in the hospital-at-home group (and the treating GPs), nursing home group and control group after 2–3 weeks); total number of days of bedridden status or hospitalisation; sleep quantity in the first 2 days after inclusion and on the 7th day as assessed by the core Consensus Sleep Diary; sleep quality, functional outcomes and QoL.^25^ Sleep quality will be assessed by the Patient-Reported Outcomes Measurement Information System (PROMIS) Sleep Disturbance short form 8b on day 7 and day 30 after inclusion.^26 27^ Functional outcomes will be measured using KATZ-15 at 30 days, 6 and 12 months.^28–30^ QoL will be assessed using EQ-5D-5L at 30 days, 6 and 12 months.^31 32^ If available, Dutch validated questionnaires are used.

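### Ordinary logistic regression is the only adjusted method named for the binary safety outcomes; with about 50 + 50 patients it is unreliable for any outcome with about 10 events or fewer

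*Protocol article*

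**What the plan says.** The Outcomes section lists the safety outcomes as "30-day mortality and occurrence of complications (readmissions, delirium, falls) within 30 days". The Data analysis plan says that secondary outcomes are established by comparing the pathway group with the control group. For categorical variables it names χ² "tests and multivariate logistic regression models". It adds "All tests of significance will be at two-tailed 0.05 level", and says that 95% confidence intervals will be used to judge whether associations are present or absent. It names no penalised or exact method.

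On size, the Sample size section says "Ideally, 50 patients will be treated outside the hospital (care pathway group) and 50 patients will be treated in the hospital (control group". On event rates, the same section gives one figure for a safety complication: "In clinical practice, approximately 10% of the hospitalised patients are readmitted to the hospital after discharge". No rate is given for mortality, delirium or falls.

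The Discussion says that group allocation follows time of day and day of the week, that illness tends to be more severe outside office hours, and that clinical outcomes are to be treated as exploratory. The strengths and limitations box says that the sample is small for effectiveness and safety.

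**The concern.** The groups are not randomised, and the article itself expects a severity difference between them. A crude comparison alone is therefore hard to interpret, and the adjusted model carries weight. Ordinary maximum-likelihood logistic regression needs events, not patients. With few events in 100 patients, two things can happen. The data can separate, so that a coefficient has no finite estimate. Or the estimate is finite but far from the truth, with very wide limits.

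At stake is whether the adjusted safety results can be used. The plan to use 95% intervals to judge the absence of an association matters most here: with sparse data, an interval that includes 1 says very little about safety.

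**Working it through.** **Inputs from the article.** 50 + 50 patients; about 10% readmission in hospitalised patients; two-sided 0.05; a hypothesis that hospitalisation is avoided in at least 75% of pathway patients, so up to 25% are hospitalised.

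**Inputs assumed.** Event rates for mortality, delirium and falls; the number and strength of covariates.

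**The plan's own figure.** The article gives no calculation for the secondary outcomes. Its 40 pathway patients belong to the primary outcome. The one-sample normal approximation n = [(z_α√(p0q0) + z_β√(p1q1))/(p0 − p1)]², with p0 = 0.90 (inferred from the 10% figure), p1 = 0.75 and two-sided 0.05, gives [(1.96×0.300 + 0.842×0.433)/0.15]² ≈ 40.3. It has no bearing on the safety comparison, except that the pathway group could end nearer 40 than 50.

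**Expected events in 100 patients.**
- 10% in both groups: 0.10×100 = 10.
- 5% in both groups: 0.05×100 = 5.
- 10% of controls, and 25% of pathway patients if a first hospitalisation counts as the equivalent event: 5 + 12.5 = 17.5.

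**Chance that at least one group has no events** (crude odds ratio zero, infinite or undefined): 1 − [1 − (1 − p)^50]².
- p = 0.05: 0.95^50 = 0.077, giving 14.8%.
- p = 0.10: 0.90^50 = 0.0052, giving 1.0%.
- With 40 + 40 patients and p = 0.05: 24%.

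**Simulation of the planned model** (50 v 50, true adjusted odds ratio 1, 1 to 6 covariates; a separated fit counts as wrong):

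| | 5% rate (about 5 events) | 10% rate (about 10 events) |
|---|---|---|
| Fit separates | about 14-17% | 1-2% |
| Odds ratio more than 4-fold wrong | about 27-37% | 8-15% |
| Wald test rejects | about 1% | 3-4% |
| Likelihood-ratio test rejects | about 8-10% | 6-8% |
| More than 4-fold wrong with Firth penalty | about 13-17% | 5-9% |

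**Sensitivity to the assumed covariates.** A second set of simulations used 2 to 8 covariates, about half of them binary, each with log odds ratio 0.4. Counting any infinite coefficient, 26-49% of fits failed at 5 events and 2-8% at 10. The group odds ratio itself was infinite in 12-15% and 1-2% (3 to 5 covariates). Likelihood-ratio rejection was 8.6-12.7% and 6.2-8.8%; Wald rejection was 0.2-0.7% and 2.2-3.7%. The pattern is the same; the size depends on the covariates.

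**Width of the intervals** (3 to 5 covariates). The median ratio of upper to lower 95% limit was about 50-90 at 5 events and 18-28 at 10. Centred on an odds ratio of 1, a ratio of 18 means limits of 1/√18 = 0.24 to √18 = 4.2. A ratio of 90 means 0.11 to 9.5.

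**More events.** At a 17.5% rate with six covariates, Wald rejected in 4.4%, likelihood-ratio in 5.7%, and 4% of odds ratios were more than 4-fold wrong. With 10% v 25%, separation occurred in about 1% or fewer.

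**Error rate of the remedy.** The Firth penalised likelihood-ratio test (3 to 5 covariates) always had a finite estimate and rejected in 2.6-3.1% at 5 events, 3.3-3.8% at 10 and 4.1-4.8% at 20. Because the true odds ratio was 1, part of the gain in 4-fold errors reflects the penalty's shrinkage towards 1.

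**The case against.** The strongest case against the point has four parts.

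1. *The event count is assumed.* This stands. The patients are older and at high risk, and rates above 10% for delirium or falls are possible. If pathway hospitalisations count as readmissions, the article's own figures give about 17 events and the problem largely disappears for that outcome.

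2. *The covariate list belongs in a statistical analysis plan.* This also stands, and its absence is not criticised. The point concerns the estimator that the article does name. A smaller model helps but does not cure the problem: the ranges above include a single covariate, and a group with no events defeats any ordinary fit.

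3. *Two stronger readings are not supported.* A reader might infer that the planned analysis will declare too many significant safety differences. That is true only of the likelihood-ratio test, and the article does not say which test is used. The interval usually reported with ordinary logistic regression is the Wald interval, which errs the other way. A reader might also infer that odds ratios will often be infinite. At the one rate the article gives, 10%, that happens in about 1-2% of studies; it becomes common only at lower, assumed rates.

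4. *The article already calls these outcomes exploratory and the sample small, and crude counts will be shown anyway.* This lowers the severity. It does not repair a model that may fail to fit, and it sits uneasily with using intervals to judge the absence of an association. Conservative Wald results are no comfort for safety outcomes, because they reduce the chance of seeing harm.

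**Conclusion.** The point holds in a conditional form. For any binary safety outcome with about 10 events or fewer in about 100 patients, the named method gives unreliable adjusted odds ratios: moderately so at about 10 events, badly so at about 5. The nominal 5% level is not met, and the article does not settle in which direction. At about 17 or more events the problem is minor.

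The conclusion rests on 50 + 50 patients from the article, and on assumed event rates of 5-10% and assumed covariate sets. Only the 10% readmission figure has a source in the text, and it is stated for hospitalised patients. The primary outcome, a single-group percentage, is unaffected. Severity is low to moderate.

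**What to change.** In the Data analysis plan, replace the ordinary logistic model for binary secondary outcomes with the following:

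- Present the crude risk difference with a Newcombe or exact 95% interval as the main result.
- Fit the adjusted model by Firth-penalised logistic regression, with profile-likelihood intervals and few, pre-named covariates. Using it for all binary secondary outcomes avoids choosing the method after seeing the event count; it also performed well at 20 events.
- A single propensity score built from the baseline data already collected is one way to keep the model small. It is not required: nearly all of the gain comes from the penalty.
- If a group has no events, rely on the crude interval.
- State that a wide interval that includes 1 is not evidence that an association is absent.

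The cost is a few sentences of wording and a little analysis time. SPSS may need an add-on or a second package for the penalised model. The estimates shrink slightly towards 1, and the intervals remain wide. No change to recruitment or data collection is needed.

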### Eligibility criteria

To be eligible to participate, a patient must meet all the following criteria: age≥65 years, clinical diagnosis of an acute moderate-to-severe (Pneumonia Severity Index (PSI) class≥3 or Confusion, Urea, Respiratory rate, Blood pressure and age≥65 years (CURB-65) score≥2) LRTI or pneumonia, an oxygen saturation≥92% and a respiratory rate≤24 breaths/minute with a maximum of 5 liters of oxygen (or adjusted oxygen saturation cut-offs as clinically indicated (eg, for patients with chronic obstructive pulmonary disease) by the physician) and written informed consent (IC) for participation.^16 17^ Exclusion criteria are: chemotherapy for solid organ malignancy (<2 months before presentation), active haematologic malignancy, immunocompromised status (eg, solid organ transplants) and/or severe dementia (Clinical Dementia Rating Scale Sum Of Boxes score 16–18).^18^ To be eligible to participate, an informal caregiver must meet all the following criteria: age≥18 years, being an informal caregiver of a patient included in the study and written IC for participation. To be eligible to participate, a treating physician must meet all the following criteria: physician of a patient included in the study at the main location of treatment, the physician should have treated the patient for at least≥2 (consecutive) days and written IC for participation.

Due to logistical limitations (absence of own GPs and evening/night/weekend shifts in nursing homes), the care pathway will be active on weekdays (Monday–Friday) between 08.00 and 18.00 hours for the hospital-at-home treatment and every day (Monday–Sunday) between 08.00 and 20.00 hours for the admission on a recovery bed in a nursing home. Patients who present at their GP and/or at the ED with an acute LRTI or pneumonia when the care pathway is active will be eligible to be treated according to the care pathway. Patients with an acute LRTI or pneumonia who are hospitalised subsequently to this ED presentation will receive the local standard of hospital care and will therefore not be included.

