#### First study visit

A research team member will visit the patient on location (at home, in the nursing home or hospital) on the first workday after the start of the treatment. During this visit, patients (and their representatives if applicable) will be able to ask additional questions about the PIL and the study. If a patient (or representative on behalf of the patient) agrees to participate, written IC will be asked for participation. In case a representative has provided written IC for an incapacitated patient (eg, in case of delirium), and the patient’s medical condition improves over time, the patient will be asked for written IC when the patient is considered competent again. When a patient has given written IC, their informal caregiver and treating physician will also be approached to participate in the study.

During this first visit, baseline information will be collected from the patient. This will include demographic information and a geriatric assessment (GA). A GA is an evidence-based, systematic procedure used to objectively describe the health status of older adults, focusing on somatic, functional and psychosocial domains; and aimed at constructing a multidisciplinary treatment plan. The GA will include the following validated tests: the Charlson Comorbidity Index, G-8 screening tool, 6-item Cognitive Impairment Test, functional status (KATZ-15 and living situation) and QoL (EQ-5D-5L).^34–36^ Ethnicity and religion are included in the demographic information as the area of The Hague has a multicultural society and these factors may influence a patient’s care system and thereby the choice of treatment location. Dementia research has shown that a considerable amount of people with a migration background makes limited use of professional homecare, and needed care is often taken over by family members.^37 38^

During this visit, patients will receive a core Consensus Sleep Diary to fill in on the 2 upcoming days and on the 7th day after inclusion. Patients will also receive a PROMIS Sleep Disturbance short form 8b to fill in on the 7th day after inclusion. The sleep quality/quantity forms will be collected 1 week after inclusion. In the hospital-at-home group, the registration forms will be collected together with the monitoring kits when the patient is released from the care pathway. See Figure 2 and Table 3 for an overview of the time points and collected data.

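### Physician satisfaction appears to be collected per patient, but the named group tests assume independent ratings; if physicians have several patients, p-values would be too small and intervals too narrow

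*Protocol article*

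**What the plan says.** The Protocol article ties each physician to a patient at every step.

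- Eligibility criteria: a participating physician is defined as "physician of a patient included in the study at the main location of treatment", and must have treated that patient for at least two days. No maximum number of patients per physician is given.
- First study visit: "When a patient has given written IC, their informal caregiver and treating physician will also be approached to participate in the study".
- Sample size: if a physician is missing, the patient stays in, and "no extra patient will be included to make up for the missing informal caregiver and/or physician".
- Study phone calls at 30 days: "At 30 days, all informal caregivers and treating physicians will receive a phone call from a research team member". They are asked about satisfaction, usability and acceptance, and "In this call, treating physicians will also be asked about the occurrence of complications".
- Table 3 and its footnote put the physician questionnaire at 30 days, on the patient's own timeline.

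The Outcomes section includes "30-day satisfaction questionnaires (patients, informal caregivers and treating physicians" in a secondary outcome. The Data analysis plan states: "The secondary outcomes will be established by comparing the patients in the care pathway group with the patients in the control group during follow-up". Satisfaction is listed there among those outcomes. The tests named are chi-square and logistic regression for categorical data. For continuous data the plan says "Differences between groups will be tested with independent t-tests or one-way Analysis Of Variance (ANOVA) tests (normal distribution", with Mann-Whitney or Kruskal-Wallis otherwise, and linear regression. All are two-tailed at 0.05. No physician-level term or exception is named.

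**The concern.** The named tests treat each questionnaire as a separate, independent observation. Two questionnaires from the same physician are not independent, because a physician who likes or dislikes a way of working will tend to say so for each patient.

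Repeats are plausible and probably uneven. Table 1 assigns a different type of physician to each setting: the GP at home, the elderly care physician in the nursing home, and the ED or ward physician in hospital. About 50 controls are to come from two hospitals, and nursing-home patients from elderly care physicians, so one physician could supply several ratings. Home patients would mostly each have their own GP. Physicians are thus largely nested within the groups compared, and that is the arrangement in which ignoring the clustering understates the standard error.

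At stake is whether a difference in physician satisfaction between settings reflects the settings or the views of a few individuals. The article lists the evaluation of physicians' satisfaction among its strengths, and its Discussion expects the results to show whether care outside the hospital satisfies them.

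**Working it through.** **The plan's own figures.** The article gives no figure for the physician ratings. Its one sample-size figure, 40 pathway patients, concerns the primary outcome. Reading the 10% readmission rate as a 90% reference against 75%, two-sided 0.05 and 80% power give [1.96 × √(0.90 × 0.10) + 0.842 × √(0.75 × 0.25)]² / 0.15² = 40.3. The stated 40 therefore reproduces closely, and this point does not touch it.

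**Inputs from the article.** 50 patients per group (Sample size); two-tailed 0.05 (Data analysis plan); physician type differs by setting (Table 1).

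**Assumptions, not in the article.** Ratings per physician, m = 1, 2 or 5; within-physician correlation, ICC = 0.1, 0.3 or 0.5; one rating per patient; each physician in one group only.

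**Formulas.**

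- Design effect: DEFF = 1 + (m − 1) × ICC
- Effective number of ratings per group: 50 / DEFF
- True two-sided error of a nominal 0.05 test: 2 × [1 − Φ(1.96 / √DEFF)]

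**Example, m = 5 and ICC = 0.5.** DEFF = 1 + 4 × 0.5 = 3. Effective n = 50 / 3 = 16.7. True error = 2 × [1 − Φ(1.96 / 1.732)] = 0.258. The nominal 95% interval would be too narrow by a factor of √3 = 1.73 and would cover about 74%.

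| m | ICC | DEFF | Effective n per group | True error, formula | True error, simulated t-test |
|---|---|---|---|---|---|
| 1 | any | 1.0 | 50 | 0.050 | 0.052 (ICC 0.3) |
| 2 | 0.1 | 1.1 | 45.5 | 0.062 | 0.061 |
| 2 | 0.3 | 1.3 | 38.5 | 0.086 | 0.086 |
| 2 | 0.5 | 1.5 | 33.3 | 0.110 | 0.109 |
| 5 | 0.1 | 1.4 | 35.7 | 0.098 | 0.096 |
| 5 | 0.3 | 2.2 | 22.7 | 0.186 | 0.192 |
| 5 | 0.5 | 3.0 | 16.7 | 0.258 | 0.267 |

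The simulations used 20,000 runs per row with no true group difference, and they agree with the formula.

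**Uneven repetition.** Suppose control physicians supply five ratings each and pathway physicians one. The average design effect is (1 + 1 + 4 × ICC) / 2 = 1.2, 1.6 and 2.0 at ICC 0.1, 0.3 and 0.5. The true error is then 0.074, 0.121 and 0.166.

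**Opposite case.** If the same physicians rated patients in both groups in balance, at ICC 0.3 the simulated error was about 0.02, so the ordinary test would be conservative. Table 1 makes this arrangement unlikely.

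**The case against.** The strongest reply is that the article never writes that a physician is questioned once per patient. Physicians are participants in their own right, with their own consent, and the sentence on the 30-day call can be read as one call each. With one rating per physician there is no problem. The comparison is also worded as one of patients, so the article does not state outright that physician ratings are tested between groups. The call asks about the pathway, which control physicians did not deliver to those patients, so a descriptive report may be all that is meant. Finally, a condensed article may leave the handling of repeated respondents to the full protocol or SAP.

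Part of this stands. A reader might infer that physicians are certainly counted several times and that the intervals are certainly too narrow. The article does not support that, because it gives no number of physicians, no ratings per physician and no correlation.

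The rest does not dispose of the point. Complications belong to one patient, and the call sits at that patient's 30 days. A physician with three patients has three such dates, so collection per patient is the natural reading, and no statement in the article contradicts it. Nor is this only an omission: the article names specific tests for an outcome that includes physician questionnaires, and those tests do not fit repeated ratings. The Discussion's caution about treating results as exploratory concerns clinical outcomes and allocation by time of day, not satisfaction.

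**Conclusion.** The point holds conditionally. Collection per patient and a between-group test are the natural reading of the article, though neither is written outright for physicians. If both apply and some physicians have several included patients, the named tests are anti-conservative. The true two-group error is 0.05 with one rating each, about 0.06 to 0.11 with two, and about 0.10 to 0.26 with five, for an ICC of 0.1 to 0.5. Both parameters are assumed, so this is a range of possibilities and not an estimate for this study.

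The consequence is small. It concerns one type of respondent within one secondary outcome. A reader should not carry it over to the feasibility percentage, the sample size or the patients' own reports, which do not depend on it.

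**What to change.** In the Data analysis plan, state whether physicians rate once or once per patient, and whether their ratings are compared between groups. If they rate per patient and are compared:

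- Record a coded physician ID with each 30-day call.
- Analyse physician-reported satisfaction with physician as the cluster, using a random physician intercept. Where physicians are few, use one mean score per physician as the unit of analysis instead.
- Report the number of distinct physicians beside the number of questionnaires in each group.

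The cost is a sentence or two in the plan and one data field. The ID is best recorded at each call. Mixed models are available in SPSS V.28, and no extra patients or contacts are needed. The downside is wider intervals for physician satisfaction.
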